#### Adaptation and re-planning

If the patient requires a repeat simulation procedure for an unforeseen reason (i.e. significant tumour reduction, atelectasis), no new SPECT/CT is performed. If the patient is in the functional avoidance arm, the baseline functional lung contours are transferred rigidly to the new planning CT, cropped to the new lung volume, and used for adaptive re-plan procedures. In case of FL volumes cannot directly be transferred and Functional Avoidance plan cannot be produced (due to large anatomical changes, atelectasis, etc), the functional volumes may be omitted in optimization. The patient may continue treatment with a standard plan. This procedure is allowed upon Specialist discretion. Site Investigator must be notified. Only the relevant treatment plan is re-optimized on the new planning CT and approved by Specialist.

### Follow-up and assessment

Participant timeline is shown in Table 1.

#### Before treatment start

All patients that meet eligibility criteria can be registered in this trial. Immediately after registration and prior to RT, baseline assessments will be made. This includes a standard physical examination, routine blood tests, SPECT/CT scan and baseline toxicity and quality of life evaluation. A baseline SPECT/CT scan will be performed < 2 weeks prior to RT. Participation in the protocol requires one extra SPECT/CT scan before initiation of RT, quality of life assessments before RT and in follow-up. Other investigations are a part of the routine clinical assessment and treatment (Table 1).

#### During treatment

The patient is seen by a physician on the day of the first, middle and last fraction, where toxicity is evaluated by CTC-AE v. 5, medication list updated, and quality of life assessed.

#### After the end of treatment (follow-up)

Follow-up visits are scheduled for 1, 3, 6, 9 and 12 months after RT. Investigations during follow-up serve the purpose of monitoring radiation-induced toxicity and quality of life. In case of lung toxicity occurrence on the scheduled follow-up visits, as well as acutely, diagnostic and treatment procedures will be done as indicated by the standard diagnostic procedures. In case of disease progression, the patient will be treated according to regular department policy.

### Statistical considerations

#### Sample size

Bases on the Quantitative Analyses of Normal Tissue Effects in the Clinic lung report and previously reported prospective trial rates [6], a freedom from RILT rate of 75% would be expected to be observed in patients receiving standard therapy. For the SPECT to be considered worthwhile for further investigation a freedom from RILT rate of at least 84% would suggest a clinically worthwhile signal in SPECT. Based on Ahern’s single arm design, a sample size of 130 patients receiving SPECT would have at least 80% power to have 95% confidence in ruling out an uninteresting freedom from RILT rate of 75% in favour of a clinically more interesting rate of 84%. In order to reduce selection bias, a randomised phase II design is proposed with a 2:1 randomisation of SPECT to standard treatment. The sample size of 195 is required and a total of 200 patients will be enrolled to offset a modest attrition rate. All patients will be followed for at least 6 months. The primary endpoint will be described by the proportion of patients in the SPECT arm are free of symptomatic RILT of at least grade 2 together with the associated 95% confidence interval. The corresponding proportion will be calculated in the control arm to provide contemporary free of symptomatic RILT of at least grade 2 rates in the standard treatment group.

It is expected that 5–6 patients per month can be accrued between the two participating countries (Denmark and Australia), thus, it is expected that accrual to this study could be completed in 3 years.

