#### Statistical analysis

Analyses will be based on the principle of intention-to-treat. Descriptive statistics will be used to summarize patient characteristics and endpoints separately in each of the treatment groups. Estimates in each group will be reported by percentage experiencing RITL together with the corresponding 95%CI.

Exploratory analyses investigating association of clinical/patient/planning factors on outcomes will be performed using standard statistical methods (t-test, multivariate regression methods, and chi-squared tests). Time-to-event outcomes will be described using the method of Kaplan-Meier and any exploratory comparisons using logrank tests and proportional hazards regression. No imputation will be made for missing data. Estimation of the relationship between DVH parameters and toxicity will be evaluated using regression methods and correlations between functional and conventional DVH parameters will be evaluated. All patients who are randomised will be included in the analysis of safety and efficacy outcomes. Any patient who is randomised but does not receive radiotherapy based on the intervention allocated treatment plan will be described in detail along with the reason for not receiving the prescribed treatment.

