#### Data safety monitoring committee and interim analysis

The data safety monitoring committee will consist of a statistician, an independent investigator, and a data manager from Clinical Trial Unit. The committee will review serious adverse events on annual basis. An interim analysis for futility is proposed to be performed after 50 patients randomised to SPECT have completed treatment and have been followed for at least 6 months. The futility boundary is determined from a likelihood ratio approach which suggest that if the ‘support’ for the interesting rate based on the likelihood ratio (84% rate: 75% rate) is LR ≤ 0.125 then the study could be considered futile in its ability to yield an estimate consistent with a freedom from RILT of at least 84%. For 50 patients, fewer than 35 patients are free from RILT, the LR ≤ 0.065. If this is observed, consideration will be given to either (i) modify the protocol (inappropriate control rate); (ii) alter the study design or (iii) stop the study. An independent Data Safety and Monitoring Committee will oversee the safety of the study as well as review the results of the 50-patient futility analysis. Otherwise, the study would proceed to recruit an additional 80 patients in Arm 1. Arm 2 would recruit in all 65 patients.

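### The primary endpoint runs to 12 months, but it is analysed as a crude proportion with 6 months' guaranteed follow-up, a 2.5% attrition allowance and no rule for incompletely followed RILT-free patients

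*Protocol article*

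**What the plan says.** Under Endpoints, the primary endpoint is the number of patients developing grade 2 or higher pulmonary toxicity, assessed serially from 1 to 12 months after radiotherapy.

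Under Sample size, the benchmark is that "a freedom from RILT rate of 75% would be expected to be observed in patients receiving standard therapy", and the target is that "a freedom from RILT rate of at least 84% would suggest a clinically worthwhile signal in SPECT". The single-arm calculation states that "a sample size of 130 patients receiving SPECT would have at least 80% power to have 95% confidence in ruling out an uninteresting" rate of 75%. Allocation is 2:1, and on the total the section says: "The sample size of 195 is required and a total of 200 patients will be enrolled to offset a modest attrition rate". It also sets a minimum follow-up of 6 months and defines the primary estimate as the proportion of SPECT patients free of RILT, with a 95% confidence interval. Expected accrual is 5 to 6 patients per month.

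Under Statistical analysis, two rules govern incomplete data: "No imputation will be made for missing data" and "All patients who are randomised will be included in the analysis of safety and efficacy outcomes". Kaplan-Meier is reserved for time-to-event outcomes, a class that does not evidently include the primary proportion.

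The section on the data safety monitoring committee and interim analysis takes Arm 1 from 50 to a further 80 patients, and for the control arm says: "Arm 2 would recruit in all 65 patients".

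**The concern.** A simple proportion needs every patient's 12-month status. A patient who dies, is lost, or reaches the analysis with less than 12 months of follow-up, all without RILT, has no such status. Keeping everyone in the denominator and imputing nothing works for that patient only if the absence of a recorded event is silently read as freedom from RILT. The other simple course, leaving the patient out, breaks the rule that all randomised patients are analysed and takes the SPECT arm towards or below the 130 that the design needs.

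At stake is whether the SPECT arm is judged to have ruled out 75%. The first course makes early loss look like absence of toxicity. The second loses information and selects patients who stayed under observation. With an allowance of about 3 SPECT patients, there is little room for either.

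**Working it through.** **Inputs from the article.** p0 = 0.75, p1 = 0.84, n = 130 in the SPECT arm, 80% power, 95% confidence, 2:1 allocation, 195 required and 200 enrolled, accrual 5–6 per month, minimum follow-up 6 months, window to 12 months.

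**Assumed.** The fraction *l* of patients with incomplete RILT-free follow-up, and the share *u* of their events that goes unseen. The article gives neither, so ranges are shown.

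**1. The plan's own figure.** An exact binomial search at one-sided 5% gives a smallest n of 130, with success at 106 or more RILT-free, error 4.9% and power 81.4%. The stated design reproduces, and 130 × 3/2 = 195.

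**2. The allowance.** (200 − 195)/200 = 2.5%. The SPECT arm of 200 is 200 × 2/3 = 133.3, about 3 above 130.

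**3. Short follow-up from the plan's own accrual.** If the analysis were run when the last patient reached 6 months (an assumption about timing), those accrued in the last 6 months would have less than 12 months: 6 × 5 = 30 to 6 × 6 = 36 patients, or 15–18% of 200. About 20–24 of them would be in the SPECT arm.

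**4. Incomplete patients counted as RILT-free.** All 133 are analysed. The exact one-sided 5% cut-off is 109, with baseline error 3.6%. The rate that appears when the truth is 75% is 1 − 0.25 × (1 − *l u*). With *u* = 0.5:

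| Incomplete *l* | Apparent rate | P(109 or more of 133) |
|---|---|---|
| 0% | 75.0% | 3.6% |
| 5% | 75.6% | 5.1% |
| 10% | 76.3% | 7.1% |
| 20% | 77.5% | 12.9% |

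If all their events were missed (*u* = 1), the error would be 12.9% at 10% and 33.1% at 20%. Power rises under this handling.

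**5. Incomplete patients dropped.** The normal approximation to power is Φ{[(p1 − p0)√n − 1.645√(p0(1 − p0))]/√(p1(1 − p1))}. For 10% loss, n = 133.3 × 0.9 = 120, which gives Φ[(0.09 × 10.954 − 1.645 × 0.4330)/0.3666] = Φ(0.75) = 77.2%.

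| Dropped | n | Approximate power | Exact power |
|---|---|---|---|
| 0% | 133 | 81.4% | 78.0% |
| 2.5% | 130 | 80.4% | 81.4% |
| 5% | 126 | 79.4% | 79.4% |
| 10% | 120 | 77.2% | 72.3% |
| 20% | 106 | 72.3% | 66.7% |

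Exact power is saw-toothed: n = 121 gives 78.5% and n = 107 gives 74.1%, so 120 and 106 are local low points. The approximate column is the fairer summary. Error stays at or below 5% here if loss is unrelated to RILT.

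**6. Arm totals.** 50 + 80 = 130 in Arm 1 and 65 in Arm 2 make 195. Enrolling 200 at 2:1 gives about 133 and 67.

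**The case against.** The strongest reply is that the article gives no death or loss rate. Its remark on poor prognosis concerns lung cancer worldwide, whereas this trial enrols patients treated with curative intent. Only patients lost before any grade 2 event matter. At 2.5% loss the design is met, and at 5% the shortfall is trivial. All of this stands, and it makes the size of the problem conditional.

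A reader might infer that the stated power and the stated error rate both fail. The documents do not support that. Dropping patients costs power but keeps the error rate if loss is non-informative; counting them as RILT-free raises error but also raises power. Nor are these the only two courses. Counting them as failures or censoring them is conceivable, and a full protocol or analysis plan, not shown, may settle it. What remains is that the rules which the article does fix (a crude proportion, everyone included, nothing imputed) do not fit together for a patient whose 12-month status is unknown.

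A reader might also take 130/65 and 200 as a contradiction. It is better read as the required number beside the enrolled number, which should be made consistent.

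Finally, deaths without RILT are not misclassified under the endpoint as worded. A competing-risks estimator also counts them as not RILT, and without censoring it equals the crude proportion. It therefore corrects for loss and short follow-up, not for deaths. That objection is sound and is why the fix has a second part.

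**Conclusion.** The point holds as a conditional one. The 2.5% allowance is unexplained, the guaranteed follow-up is half the length of the endpoint window, and the stated estimator has no place for incompletely followed RILT-free patients. With 10–20% incomplete, the consequence is either a one-sided error of about 7–13% instead of 3.6% (counted as RILT-free, half their events unseen, n = 133, cut-off 109) or power of about 77–72% (dropped). At about 5% or less it is negligible.

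The 15–18% with short follow-up follows from the plan's own accrual, but only if the analysis is run at the 6-month minimum. If it waits until every patient has reached 12 months, only deaths and losses remain. The trial is labelled non-comparative, so the harm is an optimistic or imprecise SPECT-arm rate set against 75%, not a biased test between arms.

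**What to change.** - **Primary estimate.** Replace the crude proportion by the 12-month cumulative incidence of grade 2 or higher RILT (Aalen-Johansen) in all randomised patients. Censor losses and incomplete follow-up at the last toxicity assessment and treat death without RILT as a competing event. Judge it against 75% RILT-free (25% cumulative incidence) on the one-sided 95% bound, which matches the level at which 130 reproduces. This keeps every randomised patient and imputes nothing. It does assume that censoring is unrelated to RILT, which is reasonable for late entry but less certain for drop-out.
- **Supportive analysis.** Report 12-month RILT-free survival with death as failure, in both arms, because the primary estimate still counts deaths as not RILT. Do not hold it to the 75% benchmark, which is a freedom-from-RILT rate: with 10% dying first, a true 84% would read 0.84 × 0.90 = 75.6%.
- **Sample size text.** State the assumed attrition rate and restate power at the resulting effective number (for example about 77% at 10%), instead of implying that 80% is protected. Make the 130 and 65 in the interim-analysis section consistent with the 200 enrolled.

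The cost is analysis wording and a less favourable stated power. No extra patients or visits are needed. If the sponsor preferred to hold 80%, the total would be 195/0.90 = 217 at 10% attrition or 195/0.80 = 244 at 20%.

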**Methods:**

In this study, single photon emission computed tomography (SPECT/CT) imaging technique is used for functional lung definition, in conjunction with advanced radiation dose delivery method in randomised, double-blind trial. The study aims to assess the impact of functional lung avoidance technique on pulmonary toxicity and quality of life in patients receiving chemo-RT for lung cancer. Eligibility criteria are biopsy verified lung cancer, scheduled to receive (chemo)-RT with curative intent. Every patient will undergo a pre-treatment perfusion SPECT/CT to identify functional lung. At radiation dose planning, two plans will be produced for all patients on trial. Standard reference plan, without the use of SPECT imaging data, and functional avoidance plan, will be optimised to reduce the dose to functional lung within the predefined constraints. Both plans will be clinically approved. Patients will then be randomised in a 2:1 ratio to be treated according to either the functional avoidance or the standard plan. This study aims to accrue a total of 200 patients within 3 years. The primary endpoint is symptomatic radiation-induced lung toxicity, measured serially 1–12 months after RT. Secondary endpoints include: a quality of life and patient reported lung symptoms assessment, overall survival, progression-free survival, and loco-regional disease control.

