## Methods/design

### General objective

To determine if SPECT-Perfusion Functional Avoidance improves toxicity outcomes for patients with lung cancer undergoing curative chemo-RT.

Endpoints.

The primary endpoint is symptomatic RILT, defined as number of patients developing pulmonary toxicity ≥ grade 2 in both treatment arms
Measured using the National Cancer Institute Common Toxicity Criteria (NCI-CTC) version 5 for radiation pneumonitis, dyspnea, cough, or any other radiation-induced respiratory, thoracic and mediastinal disorder. Measured serially from 1 to 12 months after RT

Secondary endpoints are:
Change in quality of life and patient reported lung symptoms according to the EORTC quality of life questionnaires QLQ-C30 and QLQ-LC-13. Measured serially from 1 to 12 months after RT.Dose-volume histogram parameters for lung and functional lungProgression-free survival, defined as time from randomisation to disease progression at any site or deathOverall survival, defined as time from randomisation to death of any cause or last date known aliveLoco-regional control rate at 12 months, defined as freedom from local disease progression 12 months after randomisation.

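### The primary endpoint runs to 12 months after RT, but the plan guarantees only 6 months' follow-up and gives the 75% and 84% rates no time horizon

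*Protocol article*

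**What the plan says.** The protocol article gives the endpoint window twice. Under General objective it reads "Measured serially from 1 to 12 months after RT", and the abstract agrees: "The primary endpoint is symptomatic radiation-induced lung toxicity, measured serially 1–12 months after RT". The visit schedule covers that window: "Follow-up visits are scheduled for 1, 3, 6, 9 and 12 months after RT", with toxicity scored at each visit in Table 1.

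The statistical sections use a shorter time. Sample size states "All patients will be followed for at least 6 months". The futility analysis is triggered "after 50 patients randomised to SPECT have completed treatment and have been followed for at least 6 months".

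The benchmarks have no time point: "a freedom from RILT rate of 75% would be expected to be observed in patients receiving standard therapy", and "a freedom from RILT rate of at least 84% would suggest a clinically worthwhile signal in SPECT". The futility likelihood ratio uses the same two rates.

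The primary result is a simple proportion free of RILT in the SPECT arm with a 95% confidence interval. Under Statistical analysis, all randomised patients are included and "No imputation will be made for missing data". Kaplan-Meier is named for time-to-event outcomes, not for this proportion.

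**The concern.** The endpoint needs 12 months of observation, and the only follow-up commitment in the statistical sections is 6. A patient who is free of RILT at 6 months, with months 6 to 12 unobserved, has no stated place in a crude proportion. If such a patient is counted as free, the observed rate can only move up.

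This matters because the decision is single-arm. The design is described as non-comparative, and SPECT is judged against a fixed 75%. The control arm supplies context but does not enter the decision, so equal truncation in both arms would not cancel. An upward shift would make a false positive signal more likely at the end and the futility look less likely to flag a poor result.

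**Working it through.** **Inputs from the article.** Benchmarks 75% and 84%; 130 SPECT patients; 2:1 allocation; accrual of 5–6 patients per month, about 3 years in all; futility count of fewer than 35 free out of 50.

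**Assumptions, because the article gives no figure.**
- A share *L* of 12-month RILT arises after month 6, spread evenly over months 6–12. *L* is taken as 20–40%.
- Accrual is uniform.
- The data are cut when the last relevant patient reaches 6 months.
- Event-free patients with under 12 months count as free.
- 75% is a 12-month rate.

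**Step 1: reproduce the plan.** With X ~ Bin(130, p) and success at X ≥ 106:
- P(X ≥ 106 | 0.75) = 0.049
- P(X ≥ 106 | 0.84) = 0.814

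So 130 patients give at least 80% power at one-sided 5%. The sample size arithmetic is right if both rates are 12-month rates and everyone is seen to 12 months.

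**Step 2: final analysis.** With 36 months' accrual and a cut 6 months after the last RT, the patients treated in the last 6 months lack full follow-up: 6/36 = 1/6, about 22 of 130. On average they miss half of the late events, so the share of all events missed is (1/6) × 0.5 × *L*. A true 75% then reads as 1 − 0.25 × (1 − missed share).

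| *L* | Missed share | 75% reads as | One-sided error at ≥106/130 |
|---|---|---|---|
| 0 | 0 | 75.0% | 4.9% |
| 20% | 1.7% | 75.4% | 6.1% |
| 30% | 2.5% | 75.6% | 6.8% |
| 40% | 3.3% | 75.8% | 7.5% |

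**Step 3: interim.** At 5–6 patients per month and 2:1 allocation, SPECT accrues 3.33–4 per month, so 50 patients take 50/4 = 12.5 to 50/3.33 = 15 months. When the fiftieth reaches 6 months, between 6/15 = 40% and 6/12.5 = 48% have under 12 months. The missed share is (0.40 to 0.48) × 0.5 × *L*.

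The futility count is fewer than 35, so the relevant probability is P(X ≤ 34) with X ~ Bin(50, p):
- full 12 months, p = 0.75: 16.3%
- *L* = 20%: p = 0.760–0.762, probability 12.5–11.8%
- *L* = 40%: p = 0.770–0.774, probability 9.3–8.1%

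The chance of crossing the stated count at a true 75% therefore falls from 16% to about 8–12%.

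**Step 4: how far the direction depends on scoring.** Suppose event-free patients with under 12 months were left out while their early events still counted. With *L* = 20%, a true 75% would read as (5/6 × 0.75) / (5/6 + 1/6 × 0.25 × 0.9) = 0.625/0.871 = 71.8%. With *L* = 40%, the 0.9 becomes 0.8 and the result is 72.1%. The bias then runs against SPECT.

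**The case against.** The strongest reply is that 6 months is a floor and not a data cut-off. Every patient has 9- and 12-month toxicity visits, and nothing says the database closes 6 months after the last RT. If the sponsor waits for the 12-month visits, the final bias disappears. This stands, and it limits the point to what the article leaves open. The article still writes down no commitment other than 6 months.

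The direction of bias is also not settled by the text. No sentence says that a patient with a partly observed window is scored as free. The no-imputation statement could be read against doing so, although all randomised patients are to be included. Step 4 shows the sign can reverse. Likewise, if 75% is in truth a rate at about 6 months, 6-month scoring would match it, and 12-month scoring would count against SPECT. Both objections stand. They make one stated horizon more necessary, because the article's result depends on choices it does not fix.

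The control arm would be truncated in the same way, so a reader could see the effect there. That helps interpretation but not the single-arm comparison with 75%. The futility rule is advisory, and a weaker futility look only lets the trial continue; it does not raise the final error.

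A reader might infer that the whole trial is to be scored at 6 months. On the same assumptions that would put one-sided error at 38–89%. The documents do not support this: the endpoint definition, Table 1 and the follow-up section all carry assessment to 12 months.

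**Conclusion.** The point holds as a mismatch of horizons with a modest likely effect. The endpoint window is 12 months, the guaranteed follow-up is 6, and the two benchmark rates have no time point, at the final analysis or at the interim. The rise in one-sided error to about 6.1–7.5%, and the fall in the interim crossing chance to about 8–12%, rest on all the assumptions listed in the working: event timing, accrual, data cut, scoring of partly observed patients, and 75% being a 12-month rate.

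A reader might go further and conclude that late RILT will be missed and the SPECT result inflated. The article does not establish that, since neither the data cut nor the scoring rule is stated. What it establishes is that a team following the text could mix follow-up lengths within one proportion and compare it with a rate of unknown horizon. It should be corrected before any analysis.

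**What to change.** 1. Replace the 6-month floor in Sample size with: *the primary analysis is done when every patient has reached the 12-month visit, or earlier death or loss to follow-up.*
2. Define the primary quantity as the proportion free of grade ≥2 RILT at 12 months after RT, with a stated rule for patients who die or are lost without RILT. A 12-month time-to-event estimate is an alternative.
3. State that 75% and 84% refer to that horizon. If their source uses another, restate the rates and recheck the sample size.
4. At the interim, score all 50 SPECT patients at one common time point, use benchmark rates for that time point, and recalculate the likelihood-ratio boundary from them. If 6 months is chosen, 6-month rates are needed; the article gives none, so no replacement count can be derived here.

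The cost is a primary analysis up to about 6 months later. The 9- and 12-month visits are already scheduled, so no new visits or procedures are needed.
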